## Methods

### Study Design

A prospective observational study will be used to measure the performance of the HRD prototype, as shown in Figure 1, in terms of time required to place it on an infant, its ability to detect HR, the speed of detection, and its reliability (accuracy) in comparison with clinical HR monitors. Given the paucity of data on infants regarding the HRD, there is insufficient evidence to support the feasibility and performance of a randomized controlled trial. The study setting will be in the postpartum unit (PPU) and neonatal intensive care unit (NICU) of a large community teaching hospital in Toronto, Canada. Specifically, the study will take place within 2 physical settings at the hospital: PPU and NICU. As shown in Figure 2, a digital camera will be used to record the HRD concurrently with either an ECG or PO monitor, depending on their availability at the time, for 3-minute durations per newborn. It is important to note that although both 3-lead ECG or photoplethysmogram technology are compared to single-lead dry-electrode ECG, both clinical devices are considered acceptable for neonatal resuscitation efforts, which is the targeted use of the HRD in later versions and research studies.

The HRD uses two 3D-printed dry electrodes to collect 3-minute single-lead neonatal ECG signals with a 500 Hz sampling rate. The HRD’s electrodes are placed approximately in the V1 and V2 locations on the newborn’s chest, as shown in Figure 3. The electrodes are developed using conductive polylactic acid filaments (Proto Pasta) and a 3D printer with printing settings of nozzle temperature at 215 °C, print speed of 35 mm/s, heated bed temperature of 60°C, and a design fill ratio of 100% [15]. These settings are chosen as specified under the datasheets provided for the conductive polylactic acid filament. As shown in Figure 4, the electrodes are connected to an ECG analog front-end circuitry, which provides analog signal processing and filtering. A 3-48 Hz analog bandpass filter is applied to attenuate the powerline and electromagnetic interference noise in the 50-60 Hz range [15]. The single-lead ECG signal is later transmitted to a microcontroller, where patent-pending embedded heart estimation techniques are used to calculate HR. HR is displayed on an OLED screen on the HRD. At the same time, the HR and raw ECG information are transmitted using Bluetooth to a nearby computer interface for data storage.

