**Objective:**

The purpose of this study is to design and examine the feasibility of a proof-of-concept HRD that quickly obtains HR using biocompatible 3D-printed dry electrodes for single-lead neonatal ECG acquisition. This study uses a novel HRD and compares it to the gold-standard 3-lead clinical ECG or PO in a hospital setting.

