A systematic review compared these different methods in terms of expense, intermittent or continuous HR assessment, and other strengths and weaknesses. Auscultation and pulse palpation are rapid and easily accessible approaches due to their low cost. However, both approaches are highly inaccurate and unreliable, resulting in errors of omission, which causes failure or delay in resuscitation steps and commission through inappropriate intervention [5]. Auscultation requires a pause in resuscitative efforts, which can disrupt the flow of resuscitation and result in a delay in stabilization of the newborn. This method is the most used approach compared to other HR determination approaches, due to its quick and easy accessibility as well as its cost-effectiveness. However, auscultation accuracy is reliant on health care professional experience and can be inconsistent from one practitioner to the other, resulting in inequitable care [6]. On the other hand, PO is relatively inexpensive and noninvasive, and it displays continuous HR and oxygen saturation to the entire team in the delivery room. However, a pulse oximeter can be inaccurate due to motion artifact, ambient light, or poor tissue perfusion, and it takes several minutes to apply and achieve the first data display, potentially delaying resuscitative efforts [4,5].

Current guidelines suggest a 3-lead ECG monitor as the gold standard for HR determination in neonates due to its high speed and accuracy and because of its capabilities to provide continuous visual and auditory data compared to the other modalities, such as PO and auscultation. However, 3-lead ECG has its disadvantages. Errors in the placement of the 3 leads can yield inappropriate ECG signals that cannot be used for HR detection [7]. Additionally, similar to PO, wet electrode ECG placement takes time to apply, surpassing the golden minute of life [5]. ECG adhesive wet electrodes can cause skin damage to premature infants. Moreover, motion artifacts may be present with ECG leads. In rare scenarios, ECG-derived HR may fail to correspond with the effective mechanical contraction of the heart [8]. Most importantly, both PO and 3-lead ECG require additional equipment, which needs to be purchased and maintained, accumulating significant expenses for health care systems [7,8]. Both technologies may not be feasible or accessible in areas with limited health care resources [9].

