The displayed HR from the HRD will be compared to 1 or 2 reference monitors, depending on the infant’s clinical setting (PPU or NICU). The PPU uses a conventional PO (Nellcor Portable SpO2 Patient Monitoring System; Medtronic) with an accompanying sensor wrap, while infants in the NICU are attached to a conventional 3-lead gel electrode ECG (Intellivue Bedside Patient Monitor; Koninklijke Philips) monitor. In both clinical-grade devices, PO and ECG biosensors and algorithms detect and display HR based on pulse peak or QRS peak detection. An internal algorithm in each device designed by the manufacturer determines how pulse or QRS peak detection is transformed into the HR displayed on the screen. Depending on the sensing technology—PO (a light-emitting diode-based pulse detection) or the 3-lead ECG (an electric activity sensing transducer that detects electrical heart activity)—a different HR may be displayed. Differences in the PO and ECG algorithmic HR estimation techniques may also influence the HR displayed on both devices. However, both technologies are known as clinical-grade HRDs and are used extensively in medical settings, which justifies their use as the ground truth state in this HRD proof-of-concept study.

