#### Data Analysis

HR and raw ECG data will be analyzed using MATLAB (the MathWorks). Infant demographics will be analyzed using summary statistics. Continuous variables will be expressed as mean (SD) values, and categorical variables will be expressed as numbers (percentages), unless otherwise stated. The HR from HRD will be compared to PO or ECG using a paired *t* test. The Bland-Altman method will be used to compare the HR derived from each device—the HRD and the PO or ECG monitor, used as reference. The correlation between devices will be assessed using Pearson *r* statistic. Data will be first analyzed using all data points available, and outliers will be defined as 20 beats per minute rate difference between the methods. These discrepancies will be further analyzed to find the likely reason for deviation, including reexamination of the video recordings.

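### Agreement of the HRD is set out against one undivided PO-or-ECG reference; read naturally, the bias and limits mix PO error with HRD error and do not isolate agreement with 3-lead ECG

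*Protocol article*

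**What the plan says.** **Choice of reference.** The protocol article describes it in several ways.

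- Study Design: "a digital camera will be used to record the HRD concurrently with either an ECG or PO monitor, depending on their availability at the time".
- Study Procedures: "The displayed HR from the HRD will be compared to 1 or 2 reference monitors", according to unit. The postpartum unit (PPU) uses PO and the NICU uses 3-lead ECG. The description of the NICU session mentions only ECG.
- Recruitment and Inclusion Criteria: NICU infants may be on ECG or on PO.

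**Analysis.** Data Analysis names the two sides of the Bland-Altman comparison as "the HRD and the PO or ECG monitor, used as reference". The paired t test is worded the same way, and Pearson r is simply between devices. The first analysis takes every available reading. Data Management counts one total of about 4500 readings over 50 infants. No analysis by reference device is described, and no number of infants per device is given.

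**The article's view of the two references.** Background calls 3-lead ECG the guideline gold standard and says that "a pulse oximeter can be inaccurate due to motion artifact, ambient light, or poor tissue perfusion". Study Procedures says that the sensing technology may lead to a different displayed rate, and adds: "Differences in the PO and ECG algorithmic HR estimation techniques may also influence the HR displayed on both devices". It accepts both as ground truth because both are clinical-grade and widely used.

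**Question asked.** The abstract's Objective says the study "compares it to the gold-standard 3-lead clinical ECG or PO in a hospital setting". The accuracy question under Objectives likewise names PO or ECG.

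**The concern.** Limits of agreement describe the difference between two specific methods. If the second method is PO in some infants and ECG in others, the spread of the differences contains HRD error, PO error in some infants, ECG error in the rest, and any systematic gap between PO and ECG. The result then depends on how many infants happened to have each monitor.

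Accuracy against clinical monitors is the main objective named in the Discussion, so this is the study's central result. A reader who wants to know how the HRD agrees with 3-lead ECG could not recover that from a combined figure. PO error would be charged to the HRD, and the same device could look better or worse under a different recruitment mix.

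Reference is also largely tied to population. PPU infants (35-week criterion) have PO. NICU infants (30-week criterion) have ECG, or ECG or PO, depending on the section read. A combined figure therefore mixes populations as well as references.

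**Working it through.** **1. The plan's own count.** 3 minutes = 180 s; 180 / 2 = 90 readings per device per infant; 90 × 50 = 4500. This reproduces the figure in Data Management. It fits one reference series per infant and is not broken down by device. The sample of 50 rests on precedent, with no formula, so it cannot be recomputed.

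**2. Effect on the limits.** The article gives no SD of differences, no PO error and no PO:ECG split, so all of these are assumed:
- SD of HRD minus ECG: 3 bpm
- PO error (PO minus ECG): independent, mean zero, SD s
- half the infants on each reference

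SD(HRD − PO) = √(3² + s²). Combined SD = √{[3² + (3² + s²)] / 2}. Half-width of the limits = 1.96 × SD.

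| s (bpm) | combined variance | combined SD | limits (bpm) |
|---|---|---|---|
| 0 | 9 | 3.00 | ±5.9 |
| 1 | (9 + 10)/2 = 9.5 | 3.08 | ±6.0 |
| 3 | (9 + 18)/2 = 13.5 | 3.67 | ±7.2 |
| 4 | (9 + 25)/2 = 17 | 4.12 | ±8.1 |
| 6 | (9 + 45)/2 = 27 | 5.20 | ±10.2 |
| 8 | (9 + 73)/2 = 41 | 6.40 | ±12.6 |

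Agreement with ECG is ±5.9 bpm in every row.

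**3. Effect of the mix.** A second set of assumptions gives ECG its own error: HRD error SD 3, ECG error SD 1, PO error SD 6, PO reading 5 bpm low, PO share p. The HRD and ECG are unbiased.

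Combined bias = 5p. Combined variance = 3² + 6²p + 1²(1 − p) + 5²p(1 − p).

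- ECG only (p = 0): bias 0; variance 10; limits ±6.2.
- p = 0.25: bias +1.25; variance 9 + 9 + 0.75 + 4.69 = 23.44; limits ±9.5.
- p = 0.50: bias +2.5; variance 9 + 18 + 0.5 + 6.25 = 33.75; limits ±11.4.
- p = 0.75: bias +3.75; variance 9 + 27 + 0.25 + 4.69 = 40.94; limits ±12.5.

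The HRD is identical in all four lines. If PO instead has the same SD as ECG (1 bpm) and no bias, the limits stay at ±6.2 for any mix and combining does no harm.

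**4. Precision after a split.** With the infant as unit, the 95% CI half-width of one limit is 1.96 × √[1/n + 1.96²/(2(n − 1))] in SD units:
- n = 50: 0.48
- n = 25: 0.68
- n = 40: 0.53
- n = 10: 1.10

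**The case against.** - **Pooling is not stated outright.** Data Analysis never says one plot or one set of limits, the PO-or-ECG wording could cover separate analyses, and an analysis plan that is not shown may contain a split. This stands as a limit on certainty. Still, one undivided reference, an analysis of all readings and a single total make pooling the natural reading.
- **No ECG-only comparison is promised.** A reader might infer that the plan fails its own objective of comparing the HRD with gold-standard ECG. The documents do not support that: the Objective and the accuracy question both name ECG or PO. What remains is that ECG is one of the two named comparators and a combined figure does not isolate it.
- **The choice is deliberate and disclosed.** Both devices are clinical-grade and acceptable for resuscitation. Infants are stable and at least 24 hours old, and filming starts once readings are stable. The remark on PO inaccuracy comes from a general review of methods, which also mentions motion artifact with ECG. All this may make PO error small, but clinical acceptability does not make two references interchangeable in an agreement analysis.
- **The effect may be small, and extra PO error makes the HRD look worse rather than better.** Fair; the low rows of the table show small effects. A reader might also infer that opposite biases could cancel to a combined bias of zero. A bias of +3 bpm against ECG and −3 against PO would do so, but it needs PO to read 6 bpm above ECG, which nothing in the documents supports. The gap would also widen the limits: with PO error SD 6, variance 27 + 0.25 × 6² = 36, so ±11.8 instead of ±10.2.
- **A split by reference is nearly a split by unit.** True. It shows the confounding with population but does not remove it.

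**Conclusion.** The point holds as a defect in how the agreement analysis is written. Followed in its natural sense, the plan gives a bias and limits of agreement that combine HRD error with PO error, vary with an unset PO:ECG mix, and leave agreement with the gold-standard ECG unisolated. The article's own statements about the two monitors are enough to show that they should not be treated as one reference.

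The size is not known. Under the assumptions above it runs from almost nothing (added PO error SD of 1 bpm) to limits about twice as wide (±12.6 against ±5.9 bpm at SD 8).

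Separately, and without any assumption, the sections disagree on which monitor is the reference: by availability in Study Design, by unit with one or two monitors in Study Procedures, ECG alone in the NICU session description, and ECG or PO for NICU infants in Recruitment and Inclusion Criteria. The article does not say which reading is analysed when two monitors are filmed.

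**What to change.** - In Data Analysis, report bias and limits of agreement separately for ECG-referenced and PO-referenced infants. Name the ECG-referenced result as the one that speaks to the gold standard, and do not headline a combined figure.
- Reconcile Study Design, Recruitment, Inclusion Criteria and Study Procedures on which monitor serves as reference in each unit. Pre-specify that the ECG reading is the analysis reference when both monitors are recorded.
- State in the report that reference is largely confounded with unit, so a difference between the two results cannot be assigned to the device alone.
- Give the expected number of infants per reference, since that sets the precision of each result.

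**Cost.** The videos already show the reference monitor, so the split needs no new data. Each group has fewer than 50 infants: at an assumed 25/25 split the CI half-width of each limit rises from about 0.48 to 0.68 SD, and at 40/10 it is 0.53 and 1.10 SD.

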**Figure 1 figure1:**
[figure not shown]
Heart rate detector (HRD) prototype. (A) The front side of the HRD with an OLED display to present heart rate in real time; (B) the backside of the HRD with two 3D-printed dry electrodes for single-lead neonatal electrocardiogram acquisition.

**Figure 2 figure2:**
[figure not shown]
Data collection setup. (A) A digital camera is used for 3-minute video recordings; (B) a pediatrician holding the heart rate detector (HRD) to the newborn’s thorax; (C) electrocardiogram monitor and (D) pulse oximetry, present in the video recordings with HRD for comparison.

**Figure 3 figure3:**
[figure not shown]
The placement of heart rate detector’s dry electrodes on the newborn's chest. HRD: heart rate detector.

**Figure 4 figure4:**

The hardware and software components of the heart rate detector (HRD).

### Study Personnel

A pediatrician and graduate student will be conducting all the study tasks.

### Recruitment

All Infants admitted to the PPU after routine delivery, regardless of method, and all infants admitted to the NICU will be eligible if their clinical status is stable and not at high risk of deterioration. In total, 50 newborns will be recruited based on previous accepted research studies that focused on examining long-term neonatal ECG and HR monitoring applications using proof-of-concept novel ECG acquisition devices [14-19].

The two groups of infants are identified as follows:

Infants admitted to the PPU who are at least 24 hours of age and are undergoing routine critical congenital heart disease (CCHD) screening with PO.Infants admitted to the NICU who are routinely placed on 3-lead ECG or PO monitors.

Recruitment steps include the following:

Infants will be identified by a pediatrician for eligibility 5 days a week (Monday to Friday) between 8 AM and 8 PM. Recruitment on Saturday and Sunday will be done if feasible. Recruitment will happen on random days when a pediatrician is available and time permits.

Once an infant is identified based on eligibility (ie, inclusion and exclusion criteria), mentioned below, the pediatrician will ask the bedside nurse to ask the parents if they would be willing to speak to the pediatrician as shown in the recruitment script in Multimedia Appendix 1.

The pediatrician will then meet the parents in a face-to-face meeting to discuss the study, provide the written consent form, and potentially obtain consent. The parents will be given at least 15 minutes to review the consent form prior to being asked to sign it. When the parents are not available at the bedside, the pediatrician will inquire the nurse about a suitable time for the parents to meet. The infants will not be under the care of the researcher pediatrician as their primary admitting health practitioner to avoid a conflict of interest.

#### Inclusion Criteria

The inclusion criteria for the PPU infants are as follows:

Corrected gestational age (35 weeks + 0 days)Infants undergoing routine CCHD screening with PO at 24 hours of life or laterStable clinical statusParental consent

For the NICU infants, the inclusion criteria are as follows:

Corrected gestational age (30 weeks + 0 days)Infants undergoing routine 3-lead continuous ECG monitoring or POInfants with at least 24 hours of lifeStable clinical status, as defined by the following: stable requirement for supplemental oxygen and stable respiratory rate on at least 2 measurements, a respiratory rate <70 breaths per minute, HR <180 beats per minute, oxygen supplementation <0.5 L/min via nasal prongs, and not being on heated high-flow oxygenParental consent

#### Exclusion Criteria

The exclusion criteria include high-risk clinically unstable newborns who might show unstable requirements for supplemental oxygen and unstable respiratory rates, congenital malformations that interfere with the placement of the HRD, and nonconsent.

The criteria mentioned above are standardized points used in multiple studies pertaining to neonatal noninvasive physiological monitoring. These criteria have undergone rigorous ethics review, as specified in the approved ethics proposals.

### Ethical Considerations

The study was approved by the research ethics boards of the Toronto Metropolitan University (2023-070) and Scarborough Health Network (PED-21-025) in April and June of 2023, respectively. Parents will complete a detailed written informed consent prior to infant enrollment. Recruitment procedures are described under the Recruitment subsection in Methods. A number of measures will be taken to protect the rights of eligible infants, including the following: (1) using an intermediate approach—a neutral person, a bedside postpartum or NICU nurse, will seek initial permission to approach potential participants about the study; (2) ensuring anonymity, privacy and confidentiality of the participant’s information; and (3) proceeding through the formal ethical review process at both the participating hospital and the university conducting the collaborative research. As per institutional policies, consent forms will be kept in a secured location, with access provided to only the primary principal investigator and then shredded. Finally, participants will be assured that the study reports, video recordings, and paper-based data collection forms will not contain identifying information in keeping with the Canadian privacy legislations—Personal Information Protection and Electronic Documents Act and Personal Health Information Protection Act.

### Study Procedures

The PPU infants will be placed in the supine (face up) position. The conventional PO will be connected to the right hand as per the device’s instructions and CCHD screening protocol. In the usual standard of care for CCHD screening, PO is placed on the right hand and right or left foot for 1 to 2 minutes. The change in the standard of care will include the data collection protocol during the time of CCHD screening, which includes video recording of the HRD and PO simultaneously. The HRD will be held in place by a pediatrician on the thorax for 3 minutes. This will prolong CCHD screening by an additional 1-3 minutes. On the other hand, as per the usual standard of care, NICU infants will be placed in the supine (face up) position prior to their usual feeding time; they will be unbundled and have their diaper changed. An already attached conventional 3-lead ECG will be placed on the infant’s chest, as per the conventional 3-lead ECG device’s instructions. The change in this standard of care will involve the thorax to be exposed, if not already exposed, and the HRD will be held in place by a pediatrician on the thorax for 3 minutes during simultaneous video recording of the HRD and the 3-lead ECG monitor. It is important to note that the 3-lead ECG electrodes will not be in contact with the HRD’s dry electrodes.

The displayed HR from the HRD will be compared to 1 or 2 reference monitors, depending on the infant’s clinical setting (PPU or NICU). The PPU uses a conventional PO (Nellcor Portable SpO2 Patient Monitoring System; Medtronic) with an accompanying sensor wrap, while infants in the NICU are attached to a conventional 3-lead gel electrode ECG (Intellivue Bedside Patient Monitor; Koninklijke Philips) monitor. In both clinical-grade devices, PO and ECG biosensors and algorithms detect and display HR based on pulse peak or QRS peak detection. An internal algorithm in each device designed by the manufacturer determines how pulse or QRS peak detection is transformed into the HR displayed on the screen. Depending on the sensing technology—PO (a light-emitting diode-based pulse detection) or the 3-lead ECG (an electric activity sensing transducer that detects electrical heart activity)—a different HR may be displayed. Differences in the PO and ECG algorithmic HR estimation techniques may also influence the HR displayed on both devices. However, both technologies are known as clinical-grade HRDs and are used extensively in medical settings, which justifies their use as the ground truth state in this HRD proof-of-concept study.

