#### Data Collection

The displayed HR from the HRD and the PO or ECG monitor will be video recorded for 3 minutes within the same video frame, as shown in Figure 1. Video recording will take place using a dedicated research digital camera mounted on a stand. Video recording will start once the infant is settled and the PO or ECG readings are stable. Stable readings are defined based on the device’s instructions on waiting for an appropriate amount of time after sensor placement for clinical HR determination. The HRD will then be placed on the infant’s chest until a consistent HR is displayed for 3 minutes, at which point video recording will start. After 3 minutes, the HRD will be removed, and then, the recording will be stopped. After the recording is completed, the entire HRD, including electrodes, will be wiped down with a surface disinfectant towelette (CaviWipe; Metrex). HRD device failure will be considered if no HR is displayed on the HRD within 60 seconds of application to the thorax.

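### The pediatrician holding the HRD works beside a live, already stable reference monitor, and one start rule leaves earlier repositioning unfilmed, so agreement could look better than the device achieves alone

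*Protocol article*

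**What the plan says.** Study Procedures has the HRD held by hand in both units. For postpartum infants: "The HRD will be held in place by a pediatrician on the thorax for 3 minutes". For NICU infants: "the HRD will be held in place by a pediatrician on the thorax for 3 minutes during simultaneous video recording of the HRD and the" reference monitor. Study Design gives the electrode positions as approximately V1 and V2. The article states no contact pressure and no rule on moving the device once it is on the chest.

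The device read-out is live and faces outward; the Figure 1 caption describes "The front side of the HRD with an OLED display to present heart rate in real time". On the reference side, Data Collection states: "The displayed HR from the HRD and the PO or ECG monitor will be video recorded for 3 minutes within the same video frame". The Figure 2 caption lists the camera, the pediatrician holding the HRD and the reference monitors as parts of one set-up.

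On sequence, Data Collection first ties the start of recording to a settled infant and a stable reference. It continues: "The HRD will then be placed on the infant’s chest until a consistent HR is displayed", and then makes that consistent display the moment when recording starts. Failure is defined as no HR displayed within 60 seconds of application.

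On staffing: "A pediatrician and graduate student will be conducting all the study tasks". Data Management takes application time and time to a steady display from the video. Data Analysis uses Bland-Altman, a paired t test and Pearson correlation, and re-examines differences of 20 beats per minute.

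**The concern.** The HRD reading depends on its operator, because two dry electrodes are pressed on by hand at approximate sites. As the set-up is described, that operator can have a trustworthy heart rate close by while placing and holding the device. If the HRD shows an implausible value, shifting it or pressing harder is a natural response, and the article neither limits nor counts such moves.

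At stake are two of the research questions in Objectives: accuracy against PO or ECG, and speed of detection. If the reference guides placement, the agreement results describe the HRD plus feedback from a clinical monitor. The intended later use is resuscitation, where the article's own argument is that conventional monitors take too long to give a reading in the first minute. Feedback of this kind would not be expected there.

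**Working it through.** **The plan's own count.** 3 minutes = 180 s; 180 / 2 = 90 readings per device per infant; 50 × 90 = 4500 per device. This reproduces the figure in Data Management and is not in dispute. The article gives no figure bearing on placement error, so the size of the effect cannot be derived from it.

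**Do the stated safeguards cover the gap?**

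- *The 60-second failure rule* applies only when no HR is shown. A displayed but wrong HR is not a failure, so adjustment may continue.
- *The 20 bpm review* sees only differences that remain in the annotated recording after any adjustment.
- *The video* covers adjustment only if it is running. Under the first start rule (reference stable, then HRD placed) it is. Under the second (consistent HRD display first) it is not. The second rule also puts the time to steady display outside the video from which Data Management measures it.
- *The raw HRD signal* is stored for the whole contact period. However, reference HR is taken from the video, and the Discussion says the monitor's raw signal is not accessible. Before filming starts, there is therefore no planned reference value to compare with.

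**Illustration of size, on assumed values.** Let the difference between devices be d = e + w. The placement error e is normal with mean 0 and SD b. The within-placement error w is normal with SD 4 bpm. The holder re-seats the device whenever |e| exceeds 5 bpm, up to k times. The half-width of the limits of agreement is 1.96 × SD(d). With no re-seating this is 1.96 × √(b² + 16): 1.96 × √25 = 9.8, 1.96 × √52 = 14.1 and 1.96 × √116 = 21.1. Simulation (200,000 draws per cell) gives:

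| Placement SD b (bpm) | No re-seat | One | Up to three | Narrowing, none to three |
|---|---|---|---|---|
| 3 | 9.8 | 9.2 | 9.1 | 1 − 9.1/9.8 = 7% |
| 6 | 14.1 | 11.6 | 9.9 | 1 − 9.9/14.1 = 30% |
| 10 | 21.1 | 17.6 | 13.3 | 1 − 13.3/21.1 = 37% |

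With b = 10, the share of differences beyond 20 bpm falls from 6.4% to 3.9% to 1.5%.

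**Upper bound, also on assumed values.** Suppose the SD is 3 bpm when the device is well placed and a share p of readings is 20 bpm off. The mixture SD is √(9 + 400p − (20p)²). For p = 0.05, 0.10 and 0.20 this is √28 = 5.29, √45 = 6.71 and √73 = 8.54, with half-widths of 10.4, 13.1 and 16.7 bpm. If every such reading were corrected, the half-width would be 1.96 × 3 = 5.9 bpm, a narrowing of 43% (1 − 5.9/10.4) to 65% (1 − 5.9/16.7).

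**The case against.** The strongest reply is that this is a journal article. Line of sight and re-seating instructions may sit in the full protocol, and silence on masking is not in itself an error. That is fair. The point rests instead on what the article does specify: hand-holding, approximate placement, a stable reference beforehand, a shared frame, and a start rule that can leave the first seconds or minutes unfilmed.

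Several stronger readings are tempting, and the documents do not support them:

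- *That the operator tunes the device until the two heart rates match.* Nothing says the holder looks at the reference or aims for a match. The start condition is consistency of the HRD display, and two researchers read the values later from video. Matching is possible but is not described.
- *That steady-display time is flattered.* Repositioning uses up time and could lengthen the interval. It would shorten it only if the clock restarted at the last placement, which the text does not say.
- *That the bias can never be removed in analysis.* Movements inside the recorded 3 minutes are on video, and errors seen there stay in the 2-second annotations. The difficulty applies to movements before filming.
- *That error is understated 1.8 to 2.8 times.* Those are the ratios behind the upper bound above. They require every bad placement to be corrected, and they treat the outlier threshold as a typical error.

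It is also true that this is an early proof-of-concept study, with resuscitation use left to later work. That limits the consequences, but accuracy remains one of its stated questions.

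**Conclusion.** The point holds in a limited form. Following the article as written, the person controlling the HRD can have the reference result available and can adjust placement before the recorded window. If that happens, agreement would tend to look better than the HRD achieves alone, and time to steady display becomes hard to interpret in either direction. On the assumed values shown, partial correction narrows the limits of agreement by roughly 7% to 37%; more than that needs near-complete correction. These figures show what could happen if re-seating is guided by the reference. They do not estimate what did happen. The contradiction between the two recording start points is documented and needs no assumption.

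**What to change.** Amend Study Procedures and Data Collection as follows:

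1. Reconcile the two start points so that filming begins once the reference is stable and before the HRD first touches the chest.
2. Where the set-up allows, shield the reference HR read-out from the holder's line of sight. Keep it visible to the camera and the second team member, with alarms audible. Base any repositioning on the HRD display alone.
3. Count and time-stamp each repositioning from the video, and run the steady-display clock from first contact. Report agreement for the first placement as well as overall.

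The cost is small: revised set-up wording, one extra column on the annotation form, slightly longer recordings and no extra staff. There are two drawbacks. The holder cannot glance at the reference HR for about 3 minutes in a stable infant. Camera framing also needs care, because both displays must stay in one frame while one is hidden from the holder. If shielding proves impractical, items 1 and 3 still make any repositioning visible and reportable.
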